**Discussion:**

This RCT will provide us information on the effect of treating MCI patients with only acupuncture, herbal formula as well as the combination of both. The additive effect or synergistic effect of acupuncture and Chinese herbal formula will then be analyzed.

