### Sample size

The calculation of the sample size in this trial was based on the change of the MoCA score. Referring to the related trial published in *BMC Complement Alternative Medicine* [7], 80% of patients with MCI showed an improvement of at least 12.5% on the MoCA score after acupuncture treatment. We assumed the rate to be 80% with one active and one control intervention, 85% with both active interventions and 60% with both control interventions. Under the assumption of a significant level of 0.05, 80% power, and 20% dropout rate, a total of 240 participants should be recruited for this RCT (60 participants in each group with 1:1:1:1 allocation).

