### Statistical analysis

An intention-to-treat (ITT) analysis will be used in this RCT. Data analyses will be performed with the use of the statistical software SPSS20.0. The baseline characteristics of the participants in the four groups will be dealt with using the chi-squared test and Fisher Exact Test for categorical data and analysis of variance for continuous variables. Intragroup comparisons will be performed via the use of paired *t* test. The main effect and the interaction effect of the two interventions will be analyzed by 2 × 2 factorial analysis of variance. The statistical significance is set at *P* < .05. All the *P* values are two-side.

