A number of studies have shown the therapeutic effect of acupuncture and CHMs, respectively, on MCI. However, RCTs with good design are still lacking, and there has not been a clinical study on the combination of the two treatments for MCI yet. Accordingly, this trial has been designed as a multi-sited RCT to evaluate the therapeutic effects of acupuncture and YSG for elderly adults with MCI. Placebo and sham acupuncture will be used to evaluate the specific effects of YSG and acupuncture rather than the placebo effect for treating MCI. The appearance and taste of the placebo granules are almost identical to the YSG, and do not contain active ingredients. Since the therapeutic effect of superficial needling cannot be excluded [38, 39], non-penetration needling will be adopted as the sham acupuncture in the trial. Several evaluation tests will be used in this trial to optimize the accuracy of the evaluation. ITT analysis will be used to reduce the bias of this RCT. The Standards for Reporting Interventions in Clinical Trials of Acupuncture (STRICTA) [40] will be followed to ensure the quality control of the acupuncture treatment.

The design of this RCT still has limitations. MCI is considered to be a kind of chronic disease, thus a total treatment of 12 weeks may not be sufficient. We will develop a more reasonable treatment cycle and follow-up period according to the results of this trial. Besides, the acupuncturist could not be blinded to the acupuncture prescription of patients and its possible effects. Therefore, the acupuncturists will be asked to avoid discussing the treatment options with patients during the entire treatment. Furthermore, we chose a standard prescription instead of personalized therapy, which may lead to performance bias. This is because the study is designed to focus on the optimal acupuncture and CHMs treatments for MCI.

This RCT should provide us with information on the effect of treating MCI patients with only acupuncture, herbal formula or as a combination of both. The additive effect or synergistic effect of acupuncture and Chinese herbal formula will then be analyzed. The findings of this RCT are expected to provide evidence for evaluating the role of Chinese traditional treatment in the treatment of MCI.

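### The article promises the effect of each therapy on its own, but the only between-group analysis it names estimates each therapy averaged over patients with and without the other

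*Protocol article*

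**What the plan says.** The article states the single-therapy question twice. The Discussion paragraph of the Abstract says: "This RCT will provide us information on the effect of treating MCI patients with only acupuncture, herbal formula as well as the combination of both". In the main Discussion, the closing paragraph says: "This RCT should provide us with information on the effect of treating MCI patients with only acupuncture, herbal formula or as a combination of both". Both go on to say that additive or synergistic effects will be analysed.

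Under Statistical analysis the between-group efficacy analysis is: "The main effect and the interaction effect of the two interventions will be analyzed by 2 × 2 factorial analysis of variance". The only other efficacy test there is a paired t test within each group, which compares no group with control. The section names no contrast between a single-therapy group and the double-control group, and gives no rule for what follows a significant or non-significant interaction.

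Under Sample size the planning rates are given: "We assumed the rate to be 80% with one active and one control intervention, 85% with both active interventions and 60% with both control interventions". They are proportions of patients with a MoCA improvement of at least 12.5%.

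The groups are A (acupuncture + YSG), B (acupuncture + placebo granules), C (sham acupuncture + YSG) and D (sham acupuncture + placebo granules).

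**The concern.** In this design the effect of acupuncture alone is B − D and the effect of YSG alone is C − D. The main effects are different quantities: (A+B)/2 − (C+D)/2 for acupuncture and (A+C)/2 − (B+D)/2 for YSG. The two pairs coincide only when the interaction is zero.

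The plan does not assume a zero interaction. On its own rates, acupuncture adds 20 points without YSG and 5 points on top of it. The trial also means to look for synergy, which is the opposite departure from additivity.

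A main effect reported as the answer to the single-therapy question can therefore mislead in either direction. With sub-additive effects it is smaller than what a patient given one therapy gains. With synergy it credits a therapy with benefit that arises only in combination.

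**Working it through.** **Inputs.** From Sample size: A = 85%, B = C = 80%, D = 60%; "Under the assumption of a significant level of 0.05, 80% power, and 20% dropout rate"; and "60 participants in each group with 1:1:1:1 allocation". From Statistical analysis: two-sided P values. Evaluable per group after dropout: 60 × 0.8 = 48.

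**1. The plan's own sample size.** The article names neither the comparison nor the formula behind 240. Of the comparisons tried, only A v D (85% v 60%) comes close. With unpooled variance, n = (1.96 + 0.8416)² × (0.85×0.15 + 0.60×0.40) / 0.25² = 7.849 × 0.3675 / 0.0625 = 46.2, so 47. Then 47/0.8 = 59 per group, 236 in total. With pooled variance it is 49, then 62 per group, 248 in total. Power for A v D at 48 per group is 79%. For comparison, 80% v 60% (one therapy against double control) needs 82 evaluable, 103 per group and 412 in total.

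**2. The two estimands under the plan's rates.**
- Acupuncture alone: B − D = 80 − 60 = 20 points. By symmetry C − D = 20 points.
- Main effect: (85+80)/2 − (80+60)/2 = 82.5 − 70.0 = 12.5 points, for either therapy.
- Interaction: A − B − C + D = 85 − 80 − 80 + 60 = −15 points.
- Check: single-therapy effect = main effect − interaction/2 = 12.5 + 7.5 = 20.

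The main effect is 12.5/20 = 62.5% of the single-therapy effect.

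**3. Precision and power at 48 per group.** The four cell variances are 0.1275, 0.16, 0.16 and 0.24; their sum is 0.6875 and their mean 0.1719.
- Main effect: SE = √(0.6875/(4×48)) = 0.0598. Power = Φ(0.125/0.0598 − 1.96) = 55%. Interval half-width 1.96 × 0.0598, about 12 points.
- B v D with the pooled ANOVA error: SE = √(2×0.1719/48) = 0.0846. Simulated power is 64%. Interval half-width 1.96 × 0.0846, about 17 points.
- B v D by a two-proportion test: power 57%.
- Interaction: SE = 2 × 0.0598 = 0.1197. Power = Φ(0.15/0.1197 − 1.96) = 24%.

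With all 60 per group analysed these become about 65%, 73%, 67% and 29%.

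**4. A synergy-only pattern (an assumption, not the plan's).** Keep 85% for A and 60% for D, and set B and C to 60%, so that neither therapy works alone. The main effect is still (85+60)/2 − (60+60)/2 = 12.5 points. Simulating the 2 × 2 ANOVA on the 0/1 response at 48 per group gives:

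| Event | Share of trials |
|---|---|
| Main effect of a given therapy significant | about 46% |
| Same, with interaction not significant | about 27% |
| Both main effects significant | about 20% |
| Interaction significant | about 47% |
| B v D significant, pooled error, either direction | about 7% |

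**The case against.** The strongest reply is that the quoted sentence plans the interaction test as well, and that test is the plan's own check on additivity. The single-therapy effect is the main effect minus half the interaction, so the planned model already contains the answer. This partly stands. Once the interaction is read alongside, the 46% in the synergy-only case falls to 27%. But power of 24% at the plan's assumed interaction makes it a weak warning, and the article does not say what would be done with the result.

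A reader might infer that each therapy will be declared effective although it does nothing alone. The documents do not support that. The plan's rates have both therapies working alone, the synergy-only pattern is an outside assumption, and even there both main effects are significant in only about one trial in five. Nor does the article state B = D or C = D as a null hypothesis. The single-therapy promise is a sentence in the Abstract and the Discussion. The aim in the Background concerns the combination, and Setting and design speaks of the efficacy of acupuncture and YSG, for which an averaged effect is a legitimate estimand.

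The 12.5 and 20 points are responder percentages, while the ANOVA is presumably run on MoCA scores; that objection stands. The power advantage of the single-therapy contrast is also thin: 64% relies on pooled error applied to binary data, the two-proportion figure is 57%, and the pooled-error contrast rejects about 7% of the time in the synergy-only case, where B = D.

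Finally, follow-up contrasts are often left to an analysis plan, and one not shown here may add them. What remains is that this text states both the question and the analysis, and the two do not match.

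**Conclusion.** The point holds as a mismatch between a promised question and a named estimand, and it is worth correcting. Factorial ANOVA is not wrong in itself. It answers what each therapy does on average over the other, while the article says it will report what each does alone.

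Under the plan's own responder rates the gap is 7.5 points (12.5 against 20). The averaged effect also has somewhat less power there, so the usual efficiency argument for main effects does not apply. These sizes belong to the responder scale; for mean MoCA scores only the direction carries over, and only if the means are sub-additive too. The synergy-only figures show that error in the other direction is possible, not that it is expected. All power figures at 48 per group assume the stated 20% dropout.

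**What to change.** Add to Statistical analysis:
- The effects of acupuncture alone and of YSG alone will be estimated from the same 2 × 2 model as B v D and C v D, with 95% confidence intervals.
- These contrasts will either be reported as estimates only or be given a stated place in the testing order.
- Main effects will be described as averaged over the other treatment.
- Any claim about one therapy by itself will rest on B v D or C v D.

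This needs no new patients, data or model. The cost is two further contrasts and wider intervals, about ±17 against ±12 points on the responder scale at 48 per group. The single-therapy contrasts would also remain short of 80% power at the planned size.

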## Methods/design

### Setting and design

A multi-sited, patient-assessor-blinded, RCT is designed to evaluate the efficacy and safety of acupuncture and the herbal formula, *Yishen* Granule (YSG), for elderly patients with mild cognitive impairment. Eligible patients will be randomly divided into four groups in a 1:1:1:1 allocation ratio, receiving acupuncture with YSG, acupuncture with placebo herbal medicine, sham acupuncture with YSG, or sham acupuncture with placebo herbal medicine. All the participants will be recruited in Shanghai Municipal Hospital of Traditional Chinese Medicine, Shanghai East Hospital, or Jingan District Hospital of Traditional Chinese Medicine. Written informed consent will be obtained from all patients. The primary outcome is scored by the Montreal Cognitive Assessment (MoCA). The secondary outcomes will be scored by the Mini-Mental State Examination (MMSE) and event-related potential (ERP). All the assessments will be conducted at baseline, and at the eighth and 12th weeks after the intervention starts. The follow-up assessments will be performed with MoCA in the 12th, 24th, and 36th weeks after intervention ends. The flowchart of the study process can be seen in Fig. 1, and the timing of treatment visits and data collection can be seen in Fig. 2 and Additional file 1.

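### The factorial ANOVA has no baseline MoCA covariate, so the main effects and interaction are estimated less precisely than the planned data allow

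*Protocol article*

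**What the plan says.** The Statistical analysis section names the model for the factorial effects: "The main effect and the interaction effect of the two interventions will be analyzed by" a 2 × 2 factorial ANOVA. The terms given are the two interventions and their interaction.

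Baseline data enter that section in two other places. Between groups, "The baseline characteristics of the participants in the four groups will be dealt with using the chi-squared test and Fisher Exact Test" for categorical data, with analysis of variance for continuous variables. Within groups, "Intragroup comparisons will be performed via the use of paired" t tests. Neither feeds into the between-group treatment estimate.

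MoCA is the primary outcome. On timing, Setting and design says: "All the assessments will be conducted at baseline, and at the eighth and 12th weeks after the intervention starts". The section on analysis does not say whether the ANOVA is applied to the raw MoCA score or to change. The Sample size section points towards change: "The calculation of the sample size in this trial was based on the change of the MoCA score". That change is then turned into the proportion of patients improving by at least 12.5%.

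**The concern.** In a cognitive trial the baseline score on the same scale is usually among the best predictors of the later score. Leaving it out of the model puts explainable between-patient variation into the error term, which widens every confidence interval. With a raw-score analysis, any chance imbalance in baseline MoCA also stays in the estimate; testing the groups for baseline differences does not remove it.

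The loss matters more here because the Discussion says the trial will examine whether the two treatments are additive or synergistic. That question is the interaction, the least precise contrast in a 2 × 2 design.

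**Working it through.** **The plan's own figure.** The only sizing figure is 240 (60 per group). It reproduces for combined treatment (85%) against double control (60%) at two-sided 0.05 and 80% power. The arcsine formula gives 47.6, so 48 per group, and 48 / 0.8 = 60. This calculation uses no SD and no correlation, so it does not show how precise the ANOVA will be.

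On the same responder rates, the marginal main effect is (60% + 80%)/2 = 70% against (80% + 85%)/2 = 82.5%. With 48 per group, power is about 53% for that main effect and 24% for the interaction on the risk-difference scale. These figures are for a binary outcome and serve only as context: the design has little precision to spare.

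**Inputs for the precision check**
- From the article: 60 per group, 20% dropout, two-sided 0.05. Hence 60 × 0.8 = 48 per group, 96 per margin and 192 in all.
- Assumed: r = 0.5 to 0.7, equal SDs at baseline and follow-up, the same r in all groups, and a main effect of 0.35 SD.

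**Formulas** (in units of the variance of one MoCA score)
- Raw-score ANOVA: error variance 1.
- Change-score ANOVA: 2(1 − r).
- ANCOVA: 1 − r².
- Ratio ANCOVA/raw = 1 − r². Ratio ANCOVA/change = (1 − r²) / [2(1 − r)] = (1 + r)/2.
- Main-effect standard error = √(2/96) × √(error variance) = 0.144 × √(error variance).
- Power = Φ(0.35 / SE − 1.96).

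**Example at r = 0.5.** Raw: 0.35 / 0.144 = 2.42, power 68%. Change: error variance 2 × 0.5 = 1, so again 68%. ANCOVA: SE = 0.144 × √0.75 = 0.125, 0.35 / 0.125 = 2.80, power 80%.

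| r | ANCOVA/raw variance | ANCOVA/change variance | Power, raw ANOVA | Power, change ANOVA | Power, ANCOVA |
|---|---|---|---|---|---|
| 0.5 | 0.75 | 0.75 | 68% | 68% | 80% |
| 0.6 | 0.64 | 0.80 | 68% | 77% | 86% |
| 0.7 | 0.51 | 0.85 | 68% | 88% | 92% |

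In sample-size terms, 192 patients under ANCOVA are worth 192 / 0.75 = 256 to 192 / 0.51 = 376 in a raw-score ANOVA. Against a change-score ANOVA they are worth 256 down to 192 / 0.85 = 226.

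**Outside that range.** At r = 0.3 the variance falls by 9% against raw and 35% against change. At r = 0.8 it falls by 64% and 10%.

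**Interaction.** The difference of differences has SE √(4/48) = 0.289 SD on the raw score, twice that of a main effect. The same ratios apply. The interaction detectable with 80% power is 2.80 × 0.289 = 0.81 SD for a raw-score ANOVA, and 0.81 × √0.75 = 0.70 SD (r = 0.5) to 0.81 × √0.51 = 0.58 SD (r = 0.7) for ANCOVA.

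**The case against.** The strongest reply is that the ANOVA may be run on change, as the Sample size section suggests. Baseline would then not be ignored, and the gain from ANCOVA would be smaller: about 12 power points at r = 0.5 and about 4 at r = 0.7 in the example above. This stands as a limit on size. It does not remove the point, because ANCOVA has lower variance than a change-score ANOVA at every r below 1, and lower variance than a raw-score ANOVA at every non-zero r.

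It is also fair to say that a factorial ANOVA suits a factorial design and gives unbiased randomised comparisons, and that covariates might be named in a plan not shown. The first is true, so this is a matter of efficiency and not validity. On the second, the article does name a method, and the method as named has no covariate.

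Two stronger readings are tempting. A reader might infer that the ANOVA drops patients without the outcome, and so contradicts "An intention-to-treat (ITT) analysis will be used in this RCT". The article does not say so. It gives no missing-data rule, an article commonly leaves that rule to the full protocol or analysis plan, and ITT and ANOVA are compatible once missing values are handled. The 20% dropout is a sample-size allowance, not an exclusion rule, and 96 per margin is used here only in that sense.

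A reader might also infer that randomisation is not stratified by hospital. The article describes central block randomisation and is silent on stratification, which is no evidence of its absence. Leaving hospital out of the model does not bias the comparison, and no between-hospital variance is given from which to compute a cost.

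**Conclusion.** The point holds as one about precision. The article fixes a factorial ANOVA without baseline MoCA, although baseline MoCA is to be collected, and this gives away precision on both main effects and the interaction. The direction is certain for any r between 0 and 1 under the equal-variance assumption. The size is not, because r, the SD and the 0.35 SD effect are all assumptions. For r from 0.5 to 0.7 the avoidable error variance is 25% to 49% if the raw score is analysed and 25% to 15% if change is analysed. The corresponding power gain in the example is 12 to 24 points or 12 to 4 points. The documents do not support a claim of bias, of a completer analysis or of a breach of ITT.

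**What to change.** In the Statistical analysis section, replace the 2 × 2 factorial ANOVA with a 2 × 2 factorial ANCOVA of post-baseline MoCA. The terms are acupuncture, YSG, acupuncture × YSG and baseline MoCA as a covariate. State that the outcome is the post-baseline score. With baseline in the model, analysing change instead gives the same treatment estimates. A hospital term is an optional secondary addition.

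The cost is a change of wording before unblinding and one degree of freedom out of roughly 190. No new data, visits or patients are needed, and the named software can fit the model.

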### Clinical trial registration

This trial is registered with Chinese Clinical Trials Registry (registration number: ChiCTR-INR-17011569, registered on 5 June 2017), and has been approved by the Ethics Committee of Shanghai Municipal Hospital of Traditional Chinese Medicine (2017SHL-KY-05).

## Discussion

It was reported that about 16% of adults diagnosed with MCI could revert back to normal or near-normal cognition approximately 1 year later [29]. However, those who reverted remain at higher risk for future cognitive decline than the individuals without a history of MCI [29]. Subjects with MCI also experience a greater mortality rate, compared with cognitively normal subjects [30]. The further development of MCI will affect the daily life of patients.

As a feasible complementary and alternative therapy, acupuncture has low side effects. We consider the regulation of the Governor Vessel to be the main acupuncture therapeutic principle of MCI. The two acupoints we chose (GV20, GV29) are two main acupoints of the Governor Vessel, which have proven to improve neurological functions. It was reported that stimulation at GV20 could alleviate the cognitive deficit and exert neuroprotective effects via modulation of the expression and processing of brain-derived neurotrophic factor in mice [31].

CHMs have long been used in China to treat cognitive decline. The YSG was developed according to the theory of “HuoXueShuGan” (invigorating the circulation of blood and smoothing the liver). *Rhizoma acori tatarinowii* and *Radix polygalae* in YSG are frequently used CHMs to treat memory impairment according to the traditional Chinese literature [32]. The extract of *Rhizoma acori tatarinowii*, which can be orally administrated, can promote the proliferation of neural progenitor cells [33]. Beta-asarone, the major active constituent of *Rhizoma acori tatarinowii*, has been shown to reverse the increase of apoptosis in the hippocampus of rats [34]. *Radix polygalae* extract, BT-11, has been reported to have memory-enhancing effects in healthy adults and in elderly humans [35, 36]. A recent study reported that polygalasaponin XXXII (PGS32), one of the active constituents of *Polygalae radix*, could attenuate scopolamine-induced cognitive impairments in mice [37].

A number of studies have shown the therapeutic effect of acupuncture and CHMs, respectively, on MCI. However, RCTs with good design are still lacking, and there has not been a clinical study on the combination of the two treatments for MCI yet. Accordingly, this trial has been designed as a multi-sited RCT to evaluate the therapeutic effects of acupuncture and YSG for elderly adults with MCI. Placebo and sham acupuncture will be used to evaluate the specific effects of YSG and acupuncture rather than the placebo effect for treating MCI. The appearance and taste of the placebo granules are almost identical to the YSG, and do not contain active ingredients. Since the therapeutic effect of superficial needling cannot be excluded [38, 39], non-penetration needling will be adopted as the sham acupuncture in the trial. Several evaluation tests will be used in this trial to optimize the accuracy of the evaluation. ITT analysis will be used to reduce the bias of this RCT. The Standards for Reporting Interventions in Clinical Trials of Acupuncture (STRICTA) [40] will be followed to ensure the quality control of the acupuncture treatment.

The design of this RCT still has limitations. MCI is considered to be a kind of chronic disease, thus a total treatment of 12 weeks may not be sufficient. We will develop a more reasonable treatment cycle and follow-up period according to the results of this trial. Besides, the acupuncturist could not be blinded to the acupuncture prescription of patients and its possible effects. Therefore, the acupuncturists will be asked to avoid discussing the treatment options with patients during the entire treatment. Furthermore, we chose a standard prescription instead of personalized therapy, which may lead to performance bias. This is because the study is designed to focus on the optimal acupuncture and CHMs treatments for MCI.

This RCT should provide us with information on the effect of treating MCI patients with only acupuncture, herbal formula or as a combination of both. The additive effect or synergistic effect of acupuncture and Chinese herbal formula will then be analyzed. The findings of this RCT are expected to provide evidence for evaluating the role of Chinese traditional treatment in the treatment of MCI.

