Chinese herbal medicine (CHM) has a long history for treating memory disorders too. Many CHMs, such as *Herba cistanches* and *Polygonum multiflorum*, have shown positive therapeutic effects on cognitive impairment [16, 17]. CHMs are usually used in combination. A placebo-controlled randomized trial showed that the Compound Chinese Medicine, *Bushen* capsule, could improve or maintain the general cognitive function of patients with AMCI during a 2-year treatment [18].

Both the acupuncture and CHMs are considered to be useful in the treatment of MCI. However, it is still unknown whether the combination of the two therapies could optimize the therapeutic effect. The aim for this RCT is to clarify the therapeutic effect of acupuncture combined with CHM for MCI.

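### The stated aim is the combination, but the only between-group analyses named are main effects and an interaction test that is weak under the plan's own rates; neither shows what the second therapy adds

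*Protocol article*

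**What the plan says.** All references are to the Protocol article.

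- **Aim.** The Background says "it is still unknown whether the combination of the two therapies could optimize the therapeutic effect" and then gives the purpose: "The aim for this RCT is to clarify the therapeutic effect of acupuncture combined with CHM for MCI".
- **Promised interpretation.** The Discussion, and the abstract in near-identical words, announces: "The additive effect or synergistic effect of acupuncture and Chinese herbal formula will then be analyzed".
- **Planned analysis.** Under Statistical analysis, "The main effect and the interaction effect of the two interventions will be analyzed by" a 2 × 2 factorial analysis of variance. The other outcome comparison is within groups: "Intragroup comparisons will be performed via the use of paired" *t* tests. All P values are two-sided. No between-group contrast of A with B, or of A with C, is named.
- **Planning rates.** Under Sample size: "We assumed the rate to be 80% with one active and one control intervention, 85% with both active interventions and 60% with both control interventions". A responder is a patient whose MoCA score improves by at least 12.5%.

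**The concern.** What the combination adds to each component is given by two simple effects: A minus B (adding the herbal formula to acupuncture) and A minus C (adding acupuncture to the herbal formula). A main effect is something else. It averages the effect of one therapy over patients who do and do not receive the other, and it equals the add-on gain only when there is no interaction.

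The plan's own rates contain an interaction, and it is negative. Two significant main effects would therefore be compatible with little benefit from adding the second therapy. The interaction test, which should warn of this, is weak at the planned size. The Discussion speaks of additive or synergistic effects, while the planning rates describe a third pattern, sub-additivity, that it does not mention. At stake is whether the trial can say anything reliable about its stated aim.

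**Working it through.** **Inputs** (Sample size and Statistical analysis sections): responder rates A 0.85, B 0.80, C 0.80, D 0.60; two-sided alpha 0.05; power 80%; dropout 20%; 60 recruited per group, so 60 × 0.8 = 48 evaluable.

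**1. The plan's own figure.** The text does not say which comparison gave 240. A versus D reproduces it with the arcsine formula:

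- h = 2·arcsin√0.85 − 2·arcsin√0.60 = 0.574
- n = 2(1.960 + 0.842)²/h² = 2 × 7.849/0.3295 = 47.6, so 48 per arm
- 48/0.8 = 60 per arm, and 4 × 60 = 240

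The pooled normal formula gives 62 per arm (248 in total) for the same contrast. With that formula the other two-sided contrasts are far off: one therapy versus double control needs 412 in total, a main effect 453, and A versus one single therapy 4,532. The number therefore fits the combination against double control, not the added benefit of combining.

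**2. Main effect against add-on gain.**

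- Gain from a therapy on top of the other: 85 − 80 = 5 points
- Gain from a therapy alone: 80 − 60 = 20 points
- Main effect: (5 + 20)/2 = 12.5 points
- Ratio of main effect to add-on gain: 12.5/5 = 2.5

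**3. What additivity would predict for group A.**

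- Risk difference: 80 + 80 − 60 = 100%
- Log odds: 2·logit(0.80) − logit(0.60) = 2 × 1.386 − 0.405 = 2.367, which is 91.4%
- Assumed: 85%, so sub-additive on both scales

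**4. Power of the interaction test at 48 per arm.**

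| | Risk difference | Logit |
|---|---|---|
| Interaction, A − B − C + D | −0.15 | −0.633 |
| Variance sum over arms | 0.1275 + 0.16 + 0.16 + 0.24 = 0.6875 | 7.84 + 6.25 + 6.25 + 4.17 = 24.51 |
| SE = √(sum/48) | 0.120 | 0.715 |
| Estimate/SE (absolute) | 1.253 | 0.885 |
| Power, Φ(z − 1.96) + Φ(−z − 1.96) | 24% | 14% |

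On the risk-difference scale the 95% CI half-width is 1.96 × 0.120 = 0.235, about 23 points. With all 60 per arm evaluable, power is 29% and 17%. For 80% power, 1,200 patients (risk difference) or 2,408 (logit) would have to be recruited.

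**5. What A minus B and A minus C can deliver.**

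- SE = √((0.1275 + 0.16)/48) = 0.0774; 0.05/0.0774 = 0.646; power about 10% (9% with a pooled variance)
- 95% CI half-width: 1.96 × 0.0774 = 0.152, about 15 points
- Both contrasts significant in favour of A: about 3.5%, by simulation
- For 80% power: 906 evaluable per arm

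**6. The continuous MoCA score.** No SD or mean difference is given, so power for the planned ANOVA cannot be computed. In SD units, the effect detectable with 80% power at 48 per arm is:

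- Main effect: 2.80 × √(1/48) = 0.40
- A minus B: 2.80 × √(2/48) = 0.57
- Interaction: 2.80 × √(4/48) = 0.81

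An interaction equal in size to a main effect that has 80% power would have Φ(2.80/2 − 1.96), about 29% power. The relative weakness of the interaction test thus carries over to the score.

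**The case against.** The strongest defence is that a 2 × 2 model with main effects and interaction is saturated. A minus B and A minus C are linear combinations of terms already in it, and a condensed article may leave such follow-up contrasts to an SAP that is not shown. The interaction test is also the standard test for synergy. This much stands, and it limits the point. Three stronger readings are tempting, and the article does not support them:

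- **That the trial formally asks whether the combination beats either therapy alone.** No such hypothesis is written. It is a reasonable reading of the Background's wording about optimizing the effect, but still a reading.
- **That the question goes untested.** The interaction test addresses synergy. Because it is two-sided it can also detect sub-additivity, and without interaction each main effect would estimate the add-on gain.
- **That a non-significant interaction will be reported as additivity.** No decision rule says so, and the Discussion sentence is not a list of permitted conclusions.

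Two further objections hold in part. The power figures concern responder proportions, whereas the primary outcome is the MoCA score and the planned method is ANOVA; each figure must be read on its stated scale. And naming the two contrasts does not supply power for them.

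What the defence does not remove is the mismatch inside the article. The Statistical analysis section states which between-group effects will be analysed. Under the Sample size section's rates, the main effects do not describe the gain from combining, and the interaction test would usually miss the departure from additivity.

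**Conclusion.** The point holds as a mismatch between aim and named analysis. Under the plan's own rates the main effect is 2.5 times the gain from adding the second therapy (12.5 against 5 points). The interaction test would miss the assumed sub-additivity about 76% of the time on the risk-difference scale and about 86% on the logit scale. A non-significant interaction would therefore be uninformative about additivity, and main effects could not stand in for the combination's added benefit.

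This rests on the assumed responder rates, 48 evaluable patients per arm and two-sided 0.05. The size of the problem on the MoCA score itself is unknown without an SD. It should be corrected before analysis; it does not invalidate the factorial design.

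**What to change.** - Pre-specify A minus B and A minus C on MoCA, at the time point designated as primary, from the same factorial model with 95% CIs, as the estimates of the combination's added benefit.
- Claim that the combination is better than its components only if both CIs exclude zero in favour of A.
- Report the interaction as an estimate with 95% CI on a named scale, state that P > .05 does not establish additivity, and name sub-additivity as a possible conclusion.
- State that at 240 patients these contrasts offer estimation rather than adequate power: about 10% each at the assumed responder rates.

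The cost is analysis wording and two contrasts from a model already planned, with no extra patients or visits. The downside is that the combination claim becomes harder to make. Adequate power for A versus one single therapy at the assumed rates would need 906 evaluable per arm, or 4,532 recruited over four arms, which wording cannot supply.
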